#### Recording AEs and SAEs

When an AE/SAE occurs, it is the responsibility of the principal investigator to review all documentation (eg, hospital notes, laboratory and diagnostic reports) related to the event. The principal investigator records all relevant information on the SAE form (if the AE meets the criteria of SAE). Information to be collected includes type of event, onset date, Investigator assessment of severity and causality, date of resolution as well as treatment required, investigations needed and outcome.

The clinician will assess all reported SAEs. The events detailed in the list below are ‘expected’ and will not be reported to the cosponsors as an SAE but will be recorded in the case report form as a hospitalisation or outcome and presented to the Data Monitoring Committee, as part of the ongoing safety review.

In this trial, the following events are not considered SAEs: (1) pregnancy is not considered an AE or SAE, as it is part of the inclusion criteria; (2) hospitalisations for treatment planned prior to randomisation and hospitalisation for elective treatment of a pre-existing condition will not be considered as an SAE. This includes pregnancy; (3) fall in haemoglobin of more than 15% between recruitment and the first postnatal day; (4) MROP in theatre; (5) need for earlier than planned MROP on the basis of the clinical condition; (6) fall in systolic or diastolic blood pressure of more than 15 mm Hg and/or increase in pulse of more than 20 beats/min between baseline and 5 min and 15 min postadministration of active/placebo treatment; (7) need for blood transfusion between time of delivery and discharge from hospital; (8)_need for general anaesthesia; (9) maternal fever (one or more temperature reading of more than 38°C within 72 hours of delivery or discharge from hospital if discharge occurs sooner); (10) sustained uterine relaxation after removal of placenta requiring uterotonics.

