#### Definitions

An AE is any untoward medical occurrence in a clinical trial participant which does not necessarily have a causal relationship with an IMP. Each AE is considered for severity, causality or expectedness and may be reclassified as a serious event.

An adverse reaction (AR) is any untoward and unintended response to the IMP which is related to any dose administered to that participant.

A serious adverse event (SAE) and serious adverse reaction (SAR) is any AE or AR that at any dose:results in death of the clinical trial participant;is life-threatening, defined as an event where the participant was at risk of death at the time of the event. It does not refer to an event which hypothetically might have caused death if it were more severe;requires inpatient hospitalisation or prolongation of existing hospitalisation;results in persistent or significant disability or incapacity;consists of a congenital anomaly or birth defect;results in any other significant medical event not meeting the criteria above.

A suspected unexpected serious adverse reaction (SUSAR) is any AR that is classified as serious and is suspected to be caused by the IMP, that it is not consistent with the information about the IMP in the summary of the medicinal product characteristics (SmPC).

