##### Assessment of expectedness

If an event is judged to be an AR, the evaluation of expectedness will be made based on knowledge of the reaction and the relevant product information documented in the SmPC. Events are classed as either expected (the AR is consistent with the toxicity of the IMP listed in the SmPC) or unexpected (the AR is not consistent with the toxicity in the SmPC).

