#### Reporting of SAEs/SAR/SUSARs

Once the investigator becomes aware that an SAE has occurred in a study participant, the information is reported to the Academic and Clinical Central Office for Research and Development (ACCORD) Research Governance and Quality Assurance Office (Edinburgh University and NHS Lothian) immediately or within 24 hours. If the Investigator does not have all information regarding an SAE, they should not wait for this additional information before notifying ACCORD. The SAE report form can be updated when the additional information is received.

The SAE report provides an assessment of causality and expectedness at the time of the initial report to ACCORD. Where missing information has not been sent to ACCORD after an initial report, ACCORD contacts the investigator and requests the missing information until this is supplied.

All reports sent to ACCORD and any follow-up information are retained by the investigator in the Investigator Site File. ACCORD also informs the trial office who check that the SAE is added to the CHaRT database.

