### Organisation: trial management, oversight and governance arrangements

#### Trial management

The trial is being jointly run by CHaRT based at the University of Aberdeen, the chief investigator and the ACCORD office at the University of Edinburgh. The trial management and governance are as recommended by The Research Governance Framework and The Medicines for Human Use (Clinical Trials) Regulations 2004. Briefly, we have set up a Trial Steering Committee and a Data Monitoring Committee led by individuals independent of the project and the institutions involved. The membership of the Trial Steering Committee includes independent members including a lay representative. A separate and independent Data Monitoring Committee has also been convened. The Data Monitoring Committee met during trial set-up to agree terms of reference and is meeting a further five times during recruitment to monitor accumulating data and oversee safety issues. The Data Monitoring Committee will meet one final time after unblinding to assess overall data validity and analyses. The Trial Steering Committee is meeting approximately seven times with the meeting spacing being matched to that of the Data Monitoring Committee. Finally, we have regular Project Management Group meetings and Research Midwives Meetings to ensure consistency of trial processes across sites and share best practice for recruitment, consent and data collection.

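### The list of events exempt from SAE status has no upper severity limit and conflicts with the SAE definition, so life-threatening instances of listed events may go unreported to the sponsor within 24 hours

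*Protocol article*

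**What the plan says.** Two sets of rules bear on the same events.

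**The exemption.** Recording AEs and SAEs introduces a ten-item list with "In this trial, the following events are not considered SAEs". The text just before it says that these events "will not be reported to the cosponsors as an SAE but will be recorded in the case report form as a hospitalisation or outcome", and that they are "presented to the Data Monitoring Committee, as part of the ongoing safety review". Items 1 and 2 concern pregnancy and planned or elective admissions. Items 3 to 10 are clinical. One example is item 6: "fall in systolic or diastolic blood pressure of more than 15 mm Hg and/or increase in pulse of more than 20 beats/min", measured from baseline to the 5 and 15 min readings.

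**The general rule.** Under Definitions, an adverse event or reaction is serious if, among other criteria, it "is life-threatening, defined as an event where the participant was at risk of death at the time of the event". Assessment of AEs and SAEs has the principal investigator judge seriousness for every adverse event, and Assessment of seriousness refers that judgement back to Definitions. Reporting of SAEs/SAR/SUSARs then requires an SAE to be sent to the sponsor's research governance office "immediately or within 24 hours".

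Neither set of rules refers to the other.

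**The concern.** Exempting expected events that are also trial outcomes is ordinary practice and is not the problem. The problem is that the exemption is written by type of event, with no limit on how grave the event may be, while the SAE definition is written by gravity, with no exception for listed types. An event that satisfies both descriptions is an SAE under one section and not an SAE under another.

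The events affected are plausible harms of the drug or of the condition. Rationale for study names symptomatic hypotension as a side effect of intravenous GTN at higher doses. Administration of study intervention gives haemorrhage, symptomatic hypotension and tachycardia as examples of side effects that lead to immediate MROP.

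At stake is whether the sponsor learns promptly of a life-threatening case, and whether such a case, if caused by the drug, enters expedited regulatory reporting. Sites that read the two rules differently would also report differently.

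**Working it through.** There is no stated figure to reproduce. The check compares the sections and tests each listed item for an upper limit.

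**Step 1. Does any clinical item have an upper severity limit?**

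| Item | Event | Limit given |
|---|---|---|
| 3 | Haemoglobin fall | Lower only (>15%) |
| 4 | MROP in theatre | None |
| 5 | Earlier MROP for clinical condition | None |
| 6 | Blood pressure fall or pulse rise at 5 and 15 min | Lower only (>15 mm Hg; >20 beats/min) |
| 7 | Transfusion before discharge | None; no volume |
| 8 | General anaesthesia | None |
| 9 | Maternal fever | Lower only (>38°C) |
| 10 | Sustained uterine relaxation needing uterotonics | None |

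Three items have a lower threshold only and five have no threshold, so 3 + 5 = 8 of 8 clinical items have no upper limit.

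**Step 2. What this means for one item.** Entry requires systolic pressure above 100 mm Hg. Assume, for illustration, a baseline of 101 mm Hg.
- Reading of 85 at 5 min: fall = 101 − 85 = 16 mm Hg, above 15, so exempt.
- Reading of 50 at 5 min: fall = 101 − 50 = 51 mm Hg, above 15, so exempt.

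The list treats the two alike. In the same way, item 3 does not separate a 16% from a 60% haemoglobin fall.

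**Step 3. Apply both rules to one event.** Take a pressure fall at the 5 min reading that puts the woman at risk of death.
- Definitions with Assessment of seriousness: an SAE.
- Reporting of SAEs/SAR/SUSARs: to the sponsor's office at once or within 24 hours.
- Recording AEs and SAEs: not an SAE, and not reported to the cosponsors as one.

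The article has no sentence that settles this.

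**Step 4. What follows if the event is drug-related.** Definitions applies the same seriousness criteria to SAEs and SARs, and a SUSAR must be classified as serious. The list speaks of SAEs only and is silent on SARs. If a site takes the list to mean that the event is not serious, the event does not become a SAR or SUSAR. It would then also miss the unblinding step in Assessment of AEs and SAEs, and the 7- and 15-day reports and annual listing in Regulatory reporting requirements. Because the list is silent on SARs, this may happen but need not.

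**Step 5. Haemorrhage.** It is not a listed item. Items 3, 5, 7 and 10 are its markers or consequences, and Administration of study intervention sends a woman with early haemorrhage to immediate MROP, which item 5 covers. One site could report a life-threatening bleed as an SAE in its own right, and another could record it only under the listed items. The text supports both.

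**The case against.** The strongest reply is that the general safeguards remain. Seriousness is assessed for every adverse event, the section containing the list itself calls for an SAE form when the SAE criteria are met, the chief investigator may upgrade an event but not downgrade one, and listed events are still recorded and reviewed. The words opening the list can be read as a deliberate trial-specific exception, and items 3 to 10 match eight of the ten secondary clinical endpoints. The article also condenses a fuller protocol.

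Much of this stands, and it rules out several stronger readings that a reader might infer.

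- *Life-threatening haemorrhage or hypotension escapes 24-hour reporting.* Not supported. Haemorrhage is not listed, and item 6 covers only the 5 and 15 min readings, so later hypotension is not exempt.
- *Fatal events are exempted.* Not supported. No listed item is a death, and death is a separate criterion in Definitions.
- *Calling the events expected bypasses the SmPC test.* Weak. Under Assessment of expectedness, "the evaluation of expectedness will be made based on knowledge of the reaction and the relevant product information documented in the SmPC", but only once an event is judged an adverse reaction. The list uses the word for events anticipated in this population.
- *Committee review replaces a 24-hour rule with a delay of months.* Not supported. The Data Monitoring Committee "is meeting a further five times during recruitment to monitor accumulating data and oversee safety issues". If its meetings follow looks about 218 women apart and 1100 women accrue evenly over 42 months, the spacing is 218 ÷ (1100 ÷ 42) = 8.3 months; over 36 months (October 2014 to September 2017) it is 218 ÷ (1100 ÷ 36) = 7.1 months. But the 24-hour rule concerns notice to the sponsor and the meetings concern committee review. These are different channels, and the interval does not measure a reporting delay.

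The replies do not remove the conflict. The seriousness assessment is one side of it, upgrading is discretionary, and reading the list as an exception would mean that life-threatening instances are indeed exempt. Nor is this a detail left to a fuller document, since the article states both rules and they disagree.

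**Conclusion.** The point holds as a conflict between two stated rules. All eight clinical items lack an upper severity limit, and the article does not say whether the list or the definition prevails when a listed event is life-threatening. Such an event may therefore go unreported to the sponsor within 24 hours and, if drug-related, may not enter the SAR/SUSAR route. For haemorrhage, the risk is inconsistent reporting between sites.

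The conclusion rests on a literal reading of the article. The full protocol, which may contain a qualifying clause, is not shown. No event rates are given, so no number of missed reports can be derived, and the documents do not show that any report has been missed. The change is worth making because the ambiguity concerns the gravest events and is easily removed.

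**What to change.** Reconcile Definitions, Recording AEs and SAEs, Assessment of seriousness, and Reporting of SAEs/SAR/SUSARs by adding one sentence to the list. It should say that the exemption does not apply when a listed event results in death, is life-threatening or causes persistent or significant disability as set out in Definitions, or is judged a serious reaction to the study drug not consistent with the SmPC, and that such events follow the ordinary SAE reporting route.

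All other listed events stay exempt, including those serious only because they prolong the hospital stay, and go to the Data Monitoring Committee as planned. The change uses the protocol's own criteria and alters no treatment rule. It costs a short protocol change, a note to sites and a few additional SAE forms.

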#### Assessment of AEs and SAEs

Seriousness, causality, severity and expectedness of each AE are assessed by the principal investigator. AEs are assessed as though the participant is taking active IMP. Cases that are considered serious, possibly, probably or definitely related to IMP and unexpected (ie, SUSARs) are unblinded. This may be delegated to other suitably qualified physicians in the research team who are trained in recording and reporting AEs. The chief investigator may not downgrade an event that has been assessed by an investigator as an SAE or SUSAR, but can upgrade an AE to an SAE, SAR or SUSAR if appropriate.

##### Assessment of seriousness

The investigator makes an assessment of seriousness as defined in Definitions section.

##### Assessment of causality

The investigator makes an assessment of whether the AE/SAE is likely to be related to the IMP according to the definitions below.Unrelated: where an event is not considered to be related to the IMP.Possibly related: the nature of the event, the underlying medical condition, concomitant medication or temporal relationship make it possible that the AE has a causal relationship to the study drug. The assessment of causality is made against the reference safety information found in the SmPC.

Where non-investigational medicinal products (NIMPs), for example, rescue/escape drugs are given: if the AE is considered to be related to an interaction between the IMP and the NIMP, or where the AE might be linked to either the IMP or the NIMP but cannot be clearly attributed to either one of these, the event will be considered as an AR. Alternative causes such as natural history of the underlying disease, other risk factors and the temporal relationship of the event to the treatment are considered and investigated; however, the blind will not be broken for the purpose of making this assessment.

##### Assessment of expectedness

If an event is judged to be an AR, the evaluation of expectedness will be made based on knowledge of the reaction and the relevant product information documented in the SmPC. Events are classed as either expected (the AR is consistent with the toxicity of the IMP listed in the SmPC) or unexpected (the AR is not consistent with the toxicity in the SmPC).

##### Assessment of severity

The investigator makes an assessment of severity for each AE/SAE and records this on the SAE form according to one of the following categories:Mild: an event that is easily tolerated by the participant, causing minimal discomfort and not interfering with every day activities.Moderate: an event that is sufficiently discomforting to interfere with normal everyday activities.Severe: an event that prevents normal everyday activities.

#### Reporting of SAEs/SAR/SUSARs

Once the investigator becomes aware that an SAE has occurred in a study participant, the information is reported to the Academic and Clinical Central Office for Research and Development (ACCORD) Research Governance and Quality Assurance Office (Edinburgh University and NHS Lothian) immediately or within 24 hours. If the Investigator does not have all information regarding an SAE, they should not wait for this additional information before notifying ACCORD. The SAE report form can be updated when the additional information is received.

The SAE report provides an assessment of causality and expectedness at the time of the initial report to ACCORD. Where missing information has not been sent to ACCORD after an initial report, ACCORD contacts the investigator and requests the missing information until this is supplied.

All reports sent to ACCORD and any follow-up information are retained by the investigator in the Investigator Site File. ACCORD also informs the trial office who check that the SAE is added to the CHaRT database.

#### Regulatory reporting requirements

The ACCORD Research Governance and Quality Assurance Office is responsible for pharmacovigilance reporting on behalf of the cosponsors (Edinburgh University and NHS Lothian). The ACCORD Research Governance and Quality Assurance Office has a legal responsibility to notify the regulatory competent authority and the Research Ethics Committee that approved the trial. Fatal or life-threatening SUSARs are reported no later than seven calendar days and all other SUSARs are reported no later than 15 calendar days after ACCORD is first aware of the reaction. ACCORD informs investigators at participating sites of all SUSARs and any other arising safety information. An Annual Safety Report/Development Safety Update Report is submitted, by ACCORD, to the regulatory authorities and Research Ethics Committees listing all SARs and SUSARs.

#### Follow-up procedures

After initially recording an AE or recording and reporting an SAE, the investigator follows each participant until resolution or death of the participant. Follow-up information on an SAE is reported to the ACCORD office. AEs still present in participants at the 6-week postnatal outcome assessment point are monitored until resolution of the event or until no longer medically indicated.

### Outcome measures

The GOT-IT trial is assessing whether sublingual GTN spray is clinically and cost-effective in treating retained placenta after vaginal delivery, reducing the need for MROP following failure of current management.

#### Primary outcome measures

The primary outcome is measured over four interrelated domains of clinical, safety, patient-sided and economic.

The primary clinical outcome is needed for MROP, defined as the placenta remaining undelivered 15 min poststudy treatment and/or being required within 15 min of treatment due to safety concerns.

The primary safety outcome is measured blood loss between administration treatment and transfer to the postnatal ward or other clinical area.

The primary patient-sided outcome is satisfaction with treatment, a side effect profile assessed by a questionnaire administered at discharge from hospital and a postal questionnaire sent to the participant 6-week posthospital discharge.

The primary economic outcome is net incremental costs (or cost savings) to the NHS of using GTN versus standard practice. Costs include GTN (dose and time to administer drug), monitoring of the woman and delivering the placenta if effective, MROP if required and further health service resource use to 6 weeks postdischarge.

### Data collection and processing

#### Collection of outcome data

The primary clinical outcome (need for MROP, defined as the placenta remaining undelivered 15 min post-treatment and/or being required within 15 min of treatment due to safety concerns) is collected 15 min postadministration of the study drug. The primary safety outcome (measured blood loss between administration treatment and transfer to the postnatal ward/other clinical area) is recorded immediately prior to transfer from theatre to the postnatal ward or other clinical area (eg, labour ward high dependency). The primary patient satisfaction outcome is collected at 6 weeks by a self-completed satisfaction questionnaire and the primary economic outcome will be computed from costs incurred at initial management of retained placenta and management of further complications and self-reported health service usage and side-effects recorded from the postnatal patient questionnaires.

Outcome data are collected on an electronic case report form and paper-based questionnaires by research midwives and nurses who have been specifically trained in data collection for the trial. The electronic case record form comprises the following sections: baseline data, clinical observations and placenta delivery, first post natal day, discharge, 6-week postnatal check, safety events, discharge and follow-up questionnaires. Health service use in the 6 weeks following discharge is collected via a small number of resource use questions included in the postnatal questionnaires. Resource use will be evaluated using routine sources of nationally relevant unit costs. Women are permitted to receive all standard care medical treatments for postpartum complications including any given for medical management of retained placenta. Concomitant medications are recorded from 24 hours prior to signing of the consent forms until 24 hours after administration of the study drug. Analgesic or antibiotic medications are recorded from 24 hours prior to signing of informed consent until 6 weeks after administration of study drug.

